## **Statement of Compliance**

The study will be carried out in accordance with Good Clinical Practice (GCP) as required by the following:

- ICH GCP E6
- Completion of Human Subjects Protection Training

## Protocol Summary

**Title:** Host and parasites factors contributing to risk of *Plasmodium* re-infection and morbidity in elementary school children in Maprik, East Sepik Province

**Population:** 500 children 5-10 years of age, who are residents of malaria-endemic villages near Maprik in the East Sepik Province, Papua New Guinea (PNG).

**Number of Sites:** 1 field site (4-8 elementary schools, Maprik District, PNG), 4 laboratory sites (Goroka & Madang PNG, Melbourne, Barcelona)

**Study Duration:** 9 months

**Subject Duration:** 9 months

### Aims:

**Aim 1:** Compare the effect of liver and blood-stage pre-treatment with blood-stage pre-treatment only on the incidence of malarial infections and disease in children 5-10 years of age.

**Aim 2:** Measure naturally acquired immune responses to both *P. falciparum* and *P. vivax* and investigate their association with subsequent risk of *P. falciparum* and *P. vivax* infection and disease in children 5-10 years of age.

### Objectives:

#### **Primary Objectives:**

- Determine the contribution of long-lasting liver-stages to risk of infection with *P. vivax* (Aim 1).
- Describe the dynamics of acquisition and loss of *P. falciparum* and *P. vivax* infections in semi-immune children (Aim 1)
- determine the extent of naturally acquired humoral and cellular immune responses to *P. falciparum* and *P. vivax* in children aged 5-10 years (Aim 2).
- determine the association of immune responses with protection against *P. falciparum* and *P. vivax* infection and disease in children aged 5-10 years (Aim 2).

**Secondary Objectives:**

- Determine the contribution of long-lasting liver-stages to risk of infection with *P. ovale* (Aim 1).
- Determine the contribution of long-lasting liver-stages to risk of clinical disease with *P. vivax* and *P. ovale* in semi-immune children (Aim 1).
- Investigate the relationship between presence of asexual and sexual stage *P. vivax* and *P. falciparum* parasites following radical cure. (Aim 1)
- Assess the effect of cumulative prior exposure to malaria on risk of acquiring new malarial infection and risk of developing clinical illness (Aim 1 & 2)
- evaluate the effect of clearing liver and blood-stage infections vs clearing blood-stage infections only on cellular and humoral immune responses. (Aim 2)
- compare cellular and humoral immune responses to *P. falciparum* and *P. vivax* in children aged 5-10 years from this region of PNG with those from children aged 5-14 years in the Mugil region of PNG. (Aim 2)

**Schematic of Study Design:** A study schedule diagram is provided in Appendix 1.

The PNGIMR recently conducted a longitudinal cohort study in children 1-3 years of age in a population near Maprik, East Sepik Province that is co-endemic for all 4 human *Plasmodium* species (MRAC 05.19). This study showed that *P. vivax* is the most prevalent malaria species in this region and contributes equally with *P. falciparum* to the burden of malarial disease in children < 3 years of age. In order to provide a baseline for the testing of both pre-erythrocytic and anti-bloodstage vaccines, the PNGIMR is in the process of completing a second study in the same cohort of children (aged 1-5 years) near Maprik. In that study children were randomised to either receive pre-treatment with artesunate and primaquine or a placebo. In addition, to these two vaccine baseline study arms a 3rd group of children received a blood stage drug (artesunate) but not a liver stage drug (primaquine) thus allowing the contribution of long lasting liver stages to the burden of infection and morbidity with *P. vivax* to be assessed. This study will not only provide the necessary baseline information for both future *P. vivax* pre-erythrocytic and blood stage vaccine trials but also allow us to determine correlates of immunity to *P. vivax* in children aged 1-5 years and to investigate the contribution of relapses to the burden of *P. vivax* in young children in an area of high *P. vivax* transmission.

However, the high level of morbidity observed in both cohorts resulted in participating children having to be treated with antimalarials very regularly during follow-up. This has made it difficult to study both the both contribution of liver-stages to burden of infection and the dynamic acquisition

and loss of malarial infections in these cohorts. In addition, the relatively low state of immunity in these young children limit investigation on immune correlates to those against clinical disease but impair our ability to determine correlates of immunity against both pre-erythrocytic and blood stage infections with either *P. falciparum* or *P. vivax*.

We therefore propose to conduct a further cohort study in slightly older children, aged 5-10 years, that will allow getting more detailed information regarding the importance of (long-lasting) liver-stages as well as naturally pre-erythrocytic and anti-blood stage immunity on subsequent rates of *Plasmodium* infection and disease in children aged 5-10 years. Such information will also be crucial for the informed design and testing of both pre-erythrocytic and erythrocytic vaccines and provide further insights correlates of (clinical) immunity to *P. falciparum* and *P. vivax* in children aged 5-10 years in a region of high *P. falciparum* and *P. vivax* transmission. Last but not least, the study will provide an opportunity to study *P. falciparum* and *P. vivax* strain dynamics without interference of frequent antimalarial treatments.

A previous study in children aged 6-12 years, conducted on the North Coast of Madang Province, showed that by 6 years of age children have acquired almost complete clinical immunity to *P. vivax* but still experience a high burden of *P. falciparum* illness, indicating that immunity to *P. vivax* is acquired significantly faster than immunity to *P. falciparum* despite similar levels of transmission (10). In this study, acquisition of immunity was characterized by increasing control of high parasite densities via both humeral and cellular immune responses (11, 12). It will be important to confirm these observations in the proposed study and investigate possible reasons for the differing speed of immune acquisition and attempt to identify both humoral and cellular correlates of immunity to both *P. falciparum* and *P. vivax*.

The proposed study will randomize children to either receive pre-treatment with chloroquine/primaquine/Coartem or chloroquine/placebo/Coartem, followed by eight months of intensive follow-up. This will therefore allow us to determine the impact of radical pre- erythrocytic / erythrocytic clearance on the subsequent burden of infection and morbidity with *P. falciparum* and *P. vivax*. Thereby, this unique study design will thus not only allow us to determine the contribution of liver-stages to the burden of malarial infection and disease but also provides an opportunity to investigate how parasite diversity and pre-erythrocytic and anti-blood stage immunity combine to influence the risk of malaria in semi-immune children

## 2.2 Rationale

This study specifically seeks to obtain important epidemiological data on the effect of radical pre-erythrocytic and erythrocytic clearance on subsequent rates of *Plasmodium* infection and disease in children aged 5-10 years using a liver-stage/blood-stage treatment to re-infection study design. In addition to this epidemiological data, the study will assess the natural acquisition of cellular and

humoral immune responses to *P. falciparum* and *P. vivax*, thus assisting in the determination of correlates of clinical immunity to *P. falciparum* and *P. vivax* in PNG children aged 5-10 years. These data will not only be essential for development of future against *P. vivax* and *P. falciparum* but provide invaluable insight into the contribution of long-lasting liver-stages to the force of infection with *P. vivax* that will contribute towards designing more rational approaches to the treatment of *P. vivax* both in the context of case management and future attempts at elimination.

## 2.3 Potential Risks and Benefits

### 2.3.1 Potential Risks

This study uses two types of anti-malarial drugs to remove blood and liver stages of malarial infections in the study children. A 3 day course of Coartem (artemeter-lumefantrine (AL)) will be used to clear blood stages in both pre-treatment arms while primaquine (PQ) will be used to eradicate liver stages in the pre-erythrocytic pre-treatment arm. In addition, a 3-day course of chloroquine will be administered to all study children at the beginning of drug treatment to assist with the clearance of blood-stages and achieve effective clearance of hypnozoites, together with primaquine, in the pre-erythrocytic arm. AL and chloroquine are well tolerated in PNG children and the schedule and dosage used in the trial correspond to the national standard treatment guidelines. Primaquine has been extensively used in the past in PNG as a gametocidal drug as well as in a short course for eradication of *P. vivax* liver stages but is rarely used today. Primaquine is generally well tolerated and has been used for the eradication of *P. vivax* liver stages in children as young as 3 months in trials of mass drug administration for the eradication of malaria in Vanuatu (13). In addition, in the recent cohort conducted in Ilaaita 150 children 1-5 years were treated with 14 days of primaquine. Detailed monitoring of side effects revealed that drug was safe and very well tolerated ([name] et al in prep). As the drug may lead to gastro-intestinal side effects (nausea etc) if not taken with food, we will give the drug with a bit of soft food prior to drug administration and actively monitor side effects during the entire duration of treatment. The use of primaquine is contraindicated in people with G-6-PD deficiency where treatment with 8-aminoquinolines may induce hemolytic anaemia. We will therefore screen all eligible study children for the presence of G-6-PD deficiency and children with less than 60% G-6-PD activity will be excluded from the study. Children with mild G-6-PD deficiency (60-80% activity) will be randomized to the two arms of the study.

Although the study objectives require frequent blood sampling, the volumes of blood collected do not represent a health risk to a normal child aged 5-10 years. Children with severe anaemia and/or severe malnutrition will however be excluded from participating in the study. Although remote, there is a small, finite risk of infection associated with finger-stick and venous blood draws. However, the Papua New Guinea Institute of Medical Research (PNGIMR) has conducted many studies involving routine finger-stick and venous blood sampling from children 5 to 10 years of age in neighboring

populations and based on our experience from these studies, very few if any study-related adverse experiences, as defined below, have occurred or been reported to us.

Venipunctures will be performed on veins in the participants' arms. Upon removal of the needle, localized bleeding is efficiently stopped with a small pressure bandage (ie, a band-aid). Participants may experience some pain as a result of the needle insertion. If the needle punctures the blood vessel, there is a risk of local bleeding that can result in minor hematoma. In order to assure the safety of participants, they will be monitored following blood draw until it can be ascertained the local bleeding has stopped. Parents and/or guardians will be instructed to take children to the study nurse based at Albinama health center in case of localized hematomas or infection at the site of needle injection who will then attend to them and if necessary refer them for further treatment. Venous blood draws will only be done by the study clinician or (pediatric) nurses with special training in drawing venous blood from small children.

As part of the study, sick children diagnosed by the study team will be referred to an IMR-run field clinic or the local health centre for treatment. Children will be treated with Coartem according to new national treatment guidelines.

The participation in this study is thus not associated with any long-term risks for study participants.

### **2.3.2 Known Potential Benefits**

The present study has potential direct benefits for the study participants and general benefits for populations in malaria endemic areas in the Southwest Pacific, Southeast Asia and South America.

For participants a potential benefit is the intensive clinical follow-up resulting in earlier diagnosis and treatment of malaria and other common childhood illnesses. In addition, children with G-6-PD deficient will be diagnosed and then counseled in regards to what drug or food the children should avoid.

For PNG and the wider scientific community the study will provide an in-depth assessment of the burden of malarial infection and disease in childhood in PNG and thereby assist in improving diagnosis and treatment. In particular, the determination of the contribution of long lasting liver stages to the burden of *P. vivax* infections and episodes will assist in re-assessing the potential use of liver stage eradication in the national antimalarial treatment guidelines and in future attempts at local malarial elimination. The close monitoring of the PQ treatment will provide important safety and efficacy data on the use of Primaquine for liver stage eradication in children 5-10 years, while the G-6-PD testing will provide data on the prevalence and severity of G-6-PD deficiency in lowland PNG.

Last but not least, the study will contribute to the development of malaria vaccines and interventions by providing an in-depth assessment of naturally acquired immunity to *P. falciparum* and *P. vivax*. The knowledge thus gained will assist in accelerating field testing of existing vaccine candidates.

### 3 AIMS & OBJECTIVES

**Aim 1: Compare the effect of liver and blood-stage pre-treatment with blood-stage pre-treatment only on the incidence of malarial infections and disease in children 5-10 years of age.**

This study aims to determine how pre-treatment with a short acting blood stage or a combination of short-acting blood stage and liver-stage drug influences the risk of subsequent malarial infections and disease in children 5-10 years of age. A 9 month longitudinal cohort study with children randomized to receive Coartem (3d), chloroquine (3d) plus either primaquine (20d) or placebo will be carried out.

**Primary Objectives:**

- Determine the contribution of long-lasting liver-stages to risk of infection with *P. vivax*.
- Describe the dynamics of acquisition and loss of *P. falciparum* and *P. vivax* infections in semi-immune children

**Secondary Objectives:**

- Determine the contribution of long-lasting liver-stages to risk of infection with *P. ovale*.
- Determine the contribution of long-lasting liver-stages to risk of clinical disease with *P. vivax* and *P. ovale* in semi-immune children.
- Investigate the relationship between presence of asexual and sexual stage *P. vivax* and *P. falciparum* parasites following radical cure.
- Assess the effect of cumulative prior exposure to malaria on risk of acquiring new malarial infection and risk of developing clinical illness

**Assessment of Aims and Objectives:**

The **first primary objective** will be addressed by determining the time-to-first *P. vivax* and *P. ovale* infection as well as the incidence of first and only infection with *P. vivax* and *P. ovale* in children that have received pre-treatment with either, blood-stage drugs alone (chloroquine/Coartem plus placebo), or blood-stage plus liver-stage drugs (chloroquine/Coartem plus primaquine) through fortnightly active case detection. By comparing the incidence in both groups it will be possible to determine the contribution of long-lasting liver-stages to the burden of infections under conditions of high transmission intensity.

The **second primary objective** will be addressed by genotyping all *P. vivax* and *P. falciparum* infection observed during the two 6-monthly follow-up periods and calculating rates of acquisition and loss as well as average duration of individual infections using methods that allow for imperfect detection and by fitting an immigration-death model to the full sequences of observations similar to the methods used by Falk et al (14). By comparing the dynamics to both *P. falciparum* and *P. vivax* as well as between the two study arms, it will be possible to determine difference between the two most common human malaria parasites in their within-host dynamics and assess the contribution of liver-stage to the dynamics of *P. vivax* infections.

**The secondary objectives will be assessed by:**

- determining the rates of clinical episodes of *P. falciparum* in children that have received pre-treatment with either, blood-stage drugs alone (chloroquine/coartem plus placebo), or blood-stage plus liver-stage drugs (chloroquine/coartem plus primaquine) through two 6-month follow-up periods.
- Determining the presence of gametocytes using light microscopy and reverse-transcriptase PCR from filter paper blood spot and comparing the prevalence of both asexual and sexual parasites in all blood samples collected.
- studying the associations between increased age and incidence of malarial infections and disease in both treatment arms.

**Aim 2: Measure naturally acquired immune responses to both *P. falciparum* and *P. vivax* and investigate their association with subsequent risk of *P. falciparum* and *P. vivax* infection and disease in children 5-10 years of age.**

This study aims to ascertain the extent of naturally acquired cellular and humoral immune responses to a range of *P. falciparum* and *P. vivax* blood pre-erythrocyte stage antigens in children 5-10 years age and determine their possible associations with protection against *P. falciparum* and *P. vivax* infections and disease. For that purpose we will measure immune responses in venous samples collected from all children after drug treatment and relate different immune measurements to risk of infection and disease during the 8 months of follow-up.

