**Table 3. Summary of scheduled study activities**

|                                       | Time                                | Activities                                                                                                                                        |
|---------------------------------------|-------------------------------------|---------------------------------------------------------------------------------------------------------------------------------------------------|
| Community information          | Start 3-4 months prior to Enrolment | - Community and school information meetings- Population Census in village schools                                                                 |
| Screening & Enrollment     | 4 weeks prior to Baseline           | - Assessment of eligibility
- Individual informed consent
- G-6-PD testing                                                                  |
| Randomisation                  | 4 weeks prior to Baseline           | - Randomisation of G-6-PD normal children to 2 arms                                                                                               |
| Drug Treatment                 | 4 weeks prior to Baseline           | - CQ/PQ/CO and CQ/PL/CO treatment regimes follow identical pattern of administration                                                              |
| Baseline                       | Week 0                              | - Baseline data collection and 10 mL venous blood sample collection                                                                               |
| Morbidity follow-up (32 weeks) | Week 2-32                           | - 2 weekly active morbidity follow-up- Continuous passive case detection- 250µl finger pricks at 2, 4, 6, 8, 10, 12, 16, 20, 24, 28 and 32 weeks. |

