## 8 ASSESSMENT OF OUTCOME MEASURES

### 8.1 Specification of the Appropriate Outcome Measures

#### 8.1.1 Primary Outcome Measures

- Time-to-first *P. vivax* and *P. falciparum* infections by LM and PCR in the 32 week follow-up period. (Aim 1)
- Incidence of first or only *P. vivax* and *P. falciparum* infection by LM and PCR during the 32 weeks of follow-up. (Aim 1)
- Incidence of clinical *P. falciparum* and *P. vivax* episodes during the 32 weeks of follow-up. (Aim 1 & 2)
- Incidence of first or only clinical *P. falciparum* and *P. vivax* episode during the 32 weeks of follow-up. (Aim 1 & 2)

Clinical *P. falciparum* and *P. vivax* malaria is defined as an axillary temperature  $\geq 37.5^{\circ}$  (or a history of fever lasting more than 2 days in duration) together with concurrent *P. falciparum* and/or *P. vivax* parasitaemia.

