### 11.2.2 Secondary Outcome Measures

The analyses for secondary *P. falciparum* infection outcomes and *P. vivax* malaria outcomes are comparable to those described for *P. vivax* infection and *P. falciparum* episodes above. The relative scarcity of *P. malariae* and *P. ovale* infections and morbidity in the proposed study age group means that the study will lack power to find any but large differences between the two arms (hazard ratio < 0.5).

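### Protocol section 3 assesses the objective on clinical *P. vivax* and *P. ovale* disease with *P. falciparum* episodes over a follow-up the design does not have, and section 11.2.2 likens *P. vivax* malaria outcomes to better-supported ones without giving an episode rate

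*Protocol*

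**What the plan says.** **Objective.** Protocol section 3, Aim 1, lists as a secondary objective: "Determine the contribution of long-lasting liver-stages to risk of clinical disease with *P. vivax* and *P. ovale* in semi-immune children".

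**Assessment in section 3.** The list of how the secondary objectives will be assessed has three items:
- "determining the rates of clinical episodes of *P. falciparum* in children" in the two arms, "through two 6-month follow-up periods";
- gametocyte detection;
- associations of age with infection and disease.

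The text on the second primary objective also refers to two 6-monthly periods.

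**Design and outcomes.** Section 4 and Table 3 give one 32-week follow-up, with "2 weekly active morbidity follow-up" from week 2 to week 32. Section 8.1.1 lists as a primary outcome: "Incidence of clinical *P. falciparum* and *P. vivax* episodes during the 32 weeks of follow-up". Section 8.1.2 lists clinical *P. ovale* episodes as secondary. Section 11.1.2.1 calls the comparison of clinical *P. falciparum* and *P. vivax* episodes between arms a primary objective. Sections 11.1.3 and 11.3.2 extend the analyses to the other species.

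**Sample size.** Section 11.2.1 claims 90% power with 500 children for a 20% decrease in *P. falciparum* episodes, assuming 0.5 per child-year. On the analyses of clinical *P. vivax*, section 11.2.2 uses the words "malaria outcomes are comparable to those described for"; the two benchmarks it names are infection with *P. vivax* and clinical episodes of *P. falciparum*. It says that only large differences (hazard ratio below 0.5) can be found for *P. malariae* and *P. ovale*.

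**Expected disease.** Section 2.1 reports that an earlier study in Madang Province "showed that by 6 years of age children have acquired almost complete clinical immunity to" *P. vivax*, with a high burden of *P. falciparum* illness remaining. Section 5.1 repeats this.

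**The concern.** Taken by itself, the assessment list in section 3 does not answer the objective above it. The protocol attributes relapse from long-lasting liver stages to *P. vivax* (section 2.1), so a comparison of *P. falciparum* episodes says little about what liver stages add to *P. vivax* or *P. ovale* disease. The stated follow-up is also impossible here: two 6-month periods make 12 months, and the study lasts 9.

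The sample-size text adds a second problem. A reader of section 11.2.2 will take clinical *P. vivax* to be about as well supported as the outcomes with a power statement, and will attach the low-power caveat only to the two rarer species. The protocol's own account of immunity suggests fewer clinical *P. vivax* episodes than *P. falciparum* episodes. Section 2.3.2 says that the liver-stage contribution to *P. vivax* infections and episodes should help in reassessing treatment guidelines, so the precision of the clinical comparison should be stated correctly.

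**Working it through.** **Step 1. The passages side by side.**

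| Item | Section 3, assessment list | Rest of the protocol |
|---|---|---|
| Species for clinical disease by arm | *P. falciparum* | *P. vivax* (8.1.1, 11.1.2.1), *P. ovale* (8.1.2, 11.1.3, 11.3.2) |
| Follow-up | Two 6-month periods | One of 32 weeks (4, Table 3, 8.1.1) |
| Rank of clinical *P. vivax* | Secondary objective | Primary in 8.1.1 and 11.1.2.1; secondary in 11.2.2 and 11.3.2 |

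The detailed clinical analysis in 11.3.1.1 also names only *P. falciparum*; *P. vivax* morbidity is reached through the cross-reference in 11.3.2.

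**Step 2. Inputs.** From the protocol: 250 per arm (500 children, equal arms), 32 weeks, 0.5 *P. falciparum* episodes per child-year, 20% decrease, 90% power. Assumed: two-sided 5% (not stated), Poisson counts, no dropout and no overdispersion. The last two assumptions favour the protocol.

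Child-years per arm = 250 × 32/52 = 153.8.

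E0 = rate × 153.8; E1 = RR × E0; SE = √(1/E0 + 1/E1); power = Φ(|ln RR|/SE − 1.96).

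**Step 3. The protocol's reference case.** At 0.5 per child-year and RR 0.80:
- E0 = 76.9 and E1 = 61.5
- SE = √(1/76.9 + 1/61.5) = 0.171
- |ln 0.80|/SE = 0.223/0.171 = 1.30
- power = Φ(1.30 − 1.96) ≈ 26%

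The stated 90% is not reproduced. A one-sided test gives 37%, and a full year of follow-up gives 38% two-sided. The section's own figures of 1.7 reduced by 60% give 1.7 × 0.4 = 0.68 per child-year, and that rate gives 33% over 32 weeks. About 1,544 children per arm would be needed for 90% power at 0.5 per child-year over 32 weeks. Among the variants tried with 250 per arm, the closest to 90% was the unreduced 1.7 per child-year over a full year (87%).

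**Step 4. Clinical *P. vivax*.** The protocol gives no rate, so a range is assumed. For a halving (RR 0.5), SE = √(3/E0) and |ln 0.5| = 0.693:

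| Assumed rate per child-year | E0, placebo arm | SE | Power |
|---|---|---|---|
| 0.05 | 7.7 | 0.624 | 20% |
| 0.10 | 15.4 | 0.442 | 35% |
| 0.20 | 30.8 | 0.312 | 60% |
| 0.25 | 38.5 | 0.279 | 70% |
| 0.50 (the *P. falciparum* rate) | 76.9 | 0.197 | 94% |

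At 300 per arm, the upper planned size, the first three rows become about 23%, 40% and 68%.

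**Step 5. Where the comparability ends.** For 90% power at RR 0.5, E0 = 3 × (1.960 + 1.282)²/0.693² ≈ 65.6. Dividing by 153.8 gives about 0.43 per child-year. Below that rate, only rate ratios under 0.5 are detectable with 90% power. This is the limit that section 11.2.2 concedes for *P. malariae* and *P. ovale* alone.

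**The case against.** A reader might infer from section 3 that the trial never compares clinical *P. vivax* or *P. ovale* disease between arms. The documents do not support that. Sections 8.1.1, 8.1.2, 11.1.2.1, 11.1.3 and 11.3.2 include these episodes, so the endpoint exists and the fault lies in section 3. It might be added that the list in section 3 does not map one item to one objective. Even so, none of its items covers this objective.

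A reader might also infer that the protocol claims 90% power for clinical *P. vivax*. It does not. The sentence in 11.2.2 has analyses as its subject and states no power, rate or detectable effect. The power reading rests on its place under sample size and on the next sentence, which is about power. That is a reasonable inference but remains an inference.

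Nor do the documents show that clinical *P. vivax* will be almost absent. The immunity statement comes from one Madang cohort aged 6-12, and section 2.1 says it needs confirming. Section 5.1 opens by saying that both species remain a significant burden at 5-10 years. Fewer *P. vivax* than *P. falciparum* episodes is a fair expectation, but its extent is unknown.

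Finally, no passage says that a null clinical result would be read as no contribution. The infection outcomes, which serve the primary objective, have their own power statement, and it does not depend on clinical episodes.

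**Conclusion.** Two things hold. First, the assessment list in section 3 names the wrong species for the objective and a follow-up that the design does not have. This contradicts sections 4, 8 and 11, and the rank of clinical *P. vivax* also differs between sections. No assumption is needed for this part.

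Second, if 11.2.2 is read as a power statement, it has no *P. vivax* episode rate behind it and fits poorly with the immunity described in 2.1 and 5.1. Over assumed rates of 0.05 to 0.25 per child-year, power for a halving is about 20% to 70%. The reference case does not rescue the comparison, since it has about 26% power for its own 20% decrease. These figures assume 250 per arm, 32 weeks, a two-sided 5% test and no dropout or overdispersion. The *P. vivax* rates are assumptions, so the size of the shortfall is a range and not a demonstrated failure.

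**What to change.** - **Section 3, secondary objectives:** name clinical *P. vivax* and *P. ovale* episodes by arm over the 32-week follow-up.
- **Section 3, second primary objective:** replace the two 6-monthly periods with the 32-week follow-up.
- **Rank:** make clinical *P. vivax* episodes either primary or secondary throughout sections 3, 8.1.1, 11.1.2.1, 11.2.2 and 11.3.2.
- **Section 11.2.2:** replace the comparability wording for *P. vivax* malaria with an assumed episode rate and its detectable rate ratio, or state that only large differences can be shown. The 90% in 11.2.1 should not serve as the reference, because it does not follow from its stated inputs.

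The cost is text changes only, with nothing altered in conduct or data collection. The downside is that the implied power for clinical *P. vivax* becomes less favourable.
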